### Study medication

Nortriptyline dosing has high inter-individual variability: the effective and tolerated daily dose ranges from < 25 mg to > 100 mg [30, 31]. To allow for this, participants will pass through an 8-week blinded dose-adjustment period to allow titration of study medication according to analgesic effect and tolerability. This process closely resembles usual clinical practice when initiating a TCA.

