### Dose-adjustment period (weeks 0–8)

All participants will receive capsules containing nortriptyline 25 mg or identical placebo capsules and will be instructed to start study medication at a dose of 1 capsule at night. Every 2 weeks the research nurse will telephone participants and record their response to the study drug: participants will be asked whether they have experienced any change in their knee pain and whether they have experienced adverse effects. Participants who have achieved satisfactory pain relief will be instructed to continue their current dose. If pain relief is inadequate and side effects are tolerated then the participant will be instructed to increase their daily dose by one capsule. If side effects are intolerable then the daily dose will be reduced by one capsule. Dose adjustment will be carried out over 8 weeks to allow participants to reach the potential maximum dose of 4 capsules daily of study medication (a potential maximum dose of 100 mg nortriptyline daily) if required and tolerated. At each of these telephone reviews adverse events will be recorded and serious adverse events (SAEs) will be immediately notified to the Clinical Review Team.

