As secondary analysis, patients will be dichotomised according to the OMERACT-OARSI set of responder criteria, defined as a high improvement in pain or function, or a moderate improvement in at least two of pain, function, or patient’s global assessment [34]. Incident rates will be calculated for this and other binary outcomes (including use of other pain medications, adverse events, and tricyclic side effects) and compared using chi-square or Fisher exact tests. Generalised linear regression models will be used to calculate absolute and relative differences in risk between treatment groups with 95 % confidence intervals, adjusting for other variables as appropriate. Self-reported treatment dosage over the past 2 weeks will be summarised for each follow-up, as will the number of participants discontinuing treatment and reasons for doing so. The incidence of all suspect serious treatment reactions will be presented in line with the CONSORT 2010 recommendations [42].

Participants who are missing outcome data will be included in the analysis using modern multiple imputation methods. To determine the robustness of results per protocol analysis will be performed, excluding participants with major protocol violations such as cross-over treatments, withdrawals and loss-to-follow-up. Dose-response will be investigated by entering final dose achieved as a predictor in regression models.

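### The dose-response analysis uses final dose as a predictor, but the titration rule makes final dose partly a consequence of pain response, so the slope is generally biased towards more dose, more pain and may reverse sign

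*Protocol article*

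**What the plan says.** The last sentence of the protocol article's section on data management and statistical analysis fixes the method: "Dose-response will be investigated by entering final dose achieved as a predictor in regression models". It does not say which arms are used, how placebo is coded, or whether treatment arm is also in the model. It does not call the result exploratory.

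The study medication section describes an "8-week blinded dose-adjustment period to allow titration of study medication according to analgesic effect and tolerability". The dose-adjustment section gives the rule. Everyone "will be instructed to start study medication at a dose of 1 capsule at night", and dose is reviewed fortnightly up to a "potential maximum dose of 4 capsules daily of study medication". At each review:

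- Hold: "Participants who have achieved satisfactory pain relief will be instructed to continue their current dose".
- Raise: "If pain relief is inadequate and side effects are tolerated then the participant will be instructed to increase their daily dose by one capsule".
- Lower: "If side effects are intolerable then the daily dose will be reduced by one capsule".

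Both arms follow the same rule, because titration is blinded. The steady-dose section then keeps each participant for six weeks on the dose reached, whether relief or side effects set it. Pain is measured at week 14.

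**The concern.** A regression of outcome on dose estimates a dose effect only if dose was not chosen in the light of the outcome. Here it was. A participant who improves, for whatever reason, stays at a low dose. One who does not improve is moved up as far as side effects allow. The regression therefore mixes the effect of dose on pain with the effect of pain on dose. The confounder is response after randomisation, so the baseline pain covariate does not deal with it.

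At stake is a misleading statement about dosing. The protocol calls this the first randomised trial of a tricyclic in osteoarthritis and expects wide clinical implications. A planned result that higher doses go with more pain could be read as evidence that raising the dose does not help, when much of it comes from the titration rule.

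**Working it through.** **The plan's own figures.** The protocol gives no figure for dose-response. Its sample size reproduces: n per group = 2(1.960 + 1.282)² × (10/5)² = 2 × 10.51 × 4 = 84.1, so 85. Allowing for 15% loss, 85/0.85 = 100. Nothing below alters this.

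**Direction of the bias.** Write week-14 pain as Y = B + P − βD + error, where B is baseline pain, P the change that would occur without drug, D the final capsules and β the true benefit per capsule. Within an arm, with the same β for everyone, the slope of Y on D given B is

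−β + Cov(P, D | B) / Var(D | B).

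The hold and raise rules send participants with poor P to higher D, so they make the covariance positive. Dose limits unrelated to P add to Var(D) and shrink the second term. Dose limits that fall mainly on participants with poor P push the covariance down. On placebo β = 0, so the slope is the artefact alone.

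**Size.** The titration rule was simulated as written: start at 1 capsule, four fortnightly reviews, hold or move by one, maximum 4. Week-14 pain was regressed on final capsules and baseline pain in the nortriptyline arm. These inputs are assumptions that the protocol does not give:

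- baseline pain about 30 (SD 7, floor 20);
- untreated change −4 (SD 8), residual SD 4;
- benefit of 1, 2 or 3 points per capsule, with three levels of variation between participants;
- adequate relief set at a 20, 30, 40 or 50% reduction;
- a 5, 10, 20, 30 or 40% chance of intolerance at each step up.

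That makes 3 × 3 × 4 × 5 = 180 scenarios.

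| Correlation of intolerance with poor prognosis | Slope positive (wrong sign) | Slope above the true value |
|---|---|---|
| 0 | 147 of 180 (82%) | 180 of 180 |
| 0.3 | 102 of 180 (57%) | 155 of 180 (86%) |
| 0.5 | 74 of 180 (41%) | 132 of 180 (73%) |

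Example with a true slope of −2 per capsule for everyone and intolerance unrelated to prognosis:

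| Intolerance per step | Slope, 30% relief threshold | Slope, 50% relief threshold |
|---|---|---|
| 5% | +2.84 | +1.61 |
| 10% | +2.07 | +0.44 |
| 20% | +1.12 | −0.52 |
| 30% | +0.54 | −0.94 |

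At the 30% threshold the bias runs from 2.84 + 2 = 4.84 down to 0.54 + 2 = 2.54 points per capsule.

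**No drug effect.** The true slope is then 0, but the nortriptyline-arm slope was +0.3 to +7.7. In the placebo arm it was +0.9 to +7.7.

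**Weak feedback from pain to dose.** With the SD of untreated change at 4 or 2 instead of 8 (true slope −2, 30% intolerance, 30% threshold), the slope was −1.20 or −1.79. That is attenuated, not reversed.

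**Capsule count entered beside treatment arm.** Two separately built simulations of a central case (1.7 points per capsule, mean tolerated dose 3.5 capsules, 30% threshold) moved the treatment coefficient from −4.4 to −1.9 and from −4.8 to −2.4.

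**The case against.** A reader might infer that this analysis is bound to give the wrong sign. The documents do not support that. Final dose also depends on tolerability, and where side effects rather than relief mainly limit dose, the slope can keep its beneficial sign. In simulated trials with 85 per arm and a true benefit of 2 points per capsule, a positive slope appeared in 98.5% at 15% intolerance per step, 76% at 30% and 44% at 50%. If intolerance goes with poor prognosis, the bias can be offset altogether.

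The model is also left open. If placebo is coded as 0 mg and there is no arm term, the slope borrows the randomised contrast and stays beneficial: it was positive in only 0.5%, 0.8% and 1.4% of the same trials. That is still not a dose-response estimate. At 30% intolerance and a 30% threshold it was −1.10 against a true −2. The distortion of the treatment coefficient arises only if capsule count sits beside arm, which the article does not say.

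A reader might also infer that the main result is at risk. It is not: the primary model contains arm and baseline pain only, and no hypothesis or listed outcome concerns dose-response.

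All of this stands, and it limits the certainty and importance of the point. It does not make the method sound. Nor is this a detail left to an analysis plan, because the article names the method.

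**Conclusion.** The stated dose-response analysis is unsound for doses titrated to response and should be changed; it affects a secondary analysis only. The existence of the bias follows from the protocol's own rule. Its size does not, because the spread of untreated change, the threshold for satisfactory relief and the rate of intolerance are all assumed. Under those assumptions the slope lies above the truth in every scenario when intolerance is unrelated to prognosis, and in most of them otherwise. Reversal of sign is common but not certain. The supported claim is a general bias towards more dose, more pain, with possible reversal, so the slope cannot inform dosing in either direction.

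**What to change.** Replace the dose-response sentence in the statistical section with text to this effect: final dose will not be used as a causal predictor of outcome and will not enter any model that estimates the treatment effect; the distribution of final capsules will be reported by arm, descriptively.

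If a dose-outcome association is still shown, label it exploratory and non-causal, and give the slope for placebo capsules beside it. That slope is a reference for the titration artefact, not an amount to subtract, since side effects will limit dose differently in the two arms.

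A per-capsule figure by instrumental variables, with randomised arm as instrument, is optional. It only rescales the intention-to-treat effect and assumes linearity and that allocation acts only through dose. When the whole benefit was simulated to occur at 1 capsule, it still returned −1.6 to −2.0 per capsule. It must carry that caveat and not be offered as evidence of a dose-response.

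The cost is a few lines of text, with no change to conduct or data collection. The trial gives up a dose-response claim that its titrated design cannot support by this method.

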### Ethical approval

The study was approved by the Northern A Health and Disability Ethics Committee. Ethics ref 14/NTA/139.

## Discussion

This protocol outlines the design of the first randomised controlled trial of a TCA in the management of OA. As there is currently a paucity of effective and safe analgesics for this common condition, the results of the study may have widespread clinical and public health implications.

## Trial status

The trial was registered with the Australian New Zealand Clinical Trials Registry on 27 June 2014. Trial identifier: ACTRN12614000683639.

Status: recruiting.

## Abbreviations

ACR: American College of Rheumatology
BMI: body mass index
CDHB: Canterbury District Health Board
CTCAE: Common Terminology Criteria for Adverse Events
GP: general practitioner
fMRI: functional magnetic resonance imaging
NSAID: non-steroidal anti-inflammatory drug
OA: osteoarthritis
OMERACT-OARSI: Outcome Measures in Rheumatology-Osteoarthritis Research Society International
PET: positron emission tomography
RCT: randomised controlled trial
SAEs: serious adverse events
SF36: 36-Item Short Form Health Survey
SNRIs: serotonin and noradrenalin reuptake inhibitors
TCA: tricyclic antidepressant
VAS: visual analogue scale
WOMAC: Western Ontario and McMaster Universities
